# 10 Eligibility

Participants must provide written, informed consent before any study procedures occur.

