# 12 Outcomes

## 12.1 Primary outcome measures

### 12.11 Program attendance

Difference in proportion of absence-free program days (AFDs) at 12 weeks from the start date of the TDTP, where ***absence-free days are defined by the cumulative number of days of program attendance during the 12-week study period.*** The potential number of AFDs for each apprentice is the cumulative number of program days that the apprentice is alive during the 12-week TDTP, with a maximum of 48 days (=12 weeks x 4 days/week). A day is defined as an 8–10-hour work-day during the TDTP from Monday to Thursday. An apprentice is considered to have attended a work-day as long as the Case Manager or their construction supervisor documents their attendance.

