# 13 Participant timeline

| Activity | Study Period (Days) | | | | |
| --- | --- | --- | --- | --- | --- |
|  | T-1 | T0 | T1 | T2 | T3 |
|  | -7 | 0 | 1-60 (M-F) | 61-70 | 800 |
| **Enrollment** | | | | | |
| Cohort Randomization | x |  |  |  |  |
| Informed Consent |  | x |  |  |  |
| Demographics |  | x |  |  |  |
| Foundational skills survey |  | x |  |  |  |
| **Interventions** | | | | | |
| Distress Thermometer screening |  |  | x |  |  |
| MH&A program |  |  | x |  |  |
| **Assessments** | | | | | |
| TDTP Attendance |  |  | x |  |  |
| TTDP Completion |  |  |  | x |  |
| Employment |  |  |  |  | x |
| Time to Access MH&A |  |  |  | x |  |
| Healthcare utilization |  |  |  | x |  |
| TDTP Satisfaction survey |  |  |  | x |  |
| Case management utilization |  |  |  | x |  |
| Distress Thermometer tool |  |  |  |  |  |
| Acceptability |  |  |  | x |  |
| Feasibility |  |  |  | x |  |
| Compliance |  |  |  | x |  |

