# 15 Recruitment

To be eligible for TDTP enrollment, individuals must be Canadian, female, black, from a racialized community, an immigrant, and/or Indigenous. Eligible individuals must submit to an interview with Community Builders®. Successful candidates must demonstrate that they are a good fit for the TDTP by showing, at a minimum, an interest in the construction trades and possessing some basic English or French-speaking and writing skills. Enrollment in the TDTP is not contingent on eligible individuals agreeing to participate in the TeachMeToBuild study. Individuals enrolled in the TDTP whose cohort is randomized to the Distress Thermometer screening tool intervention will be introduced to the TeachMeToBuild study during their initial TDTP orientation. The case managers will use the expressed consent powerpoint presentation to introduce the study to the students. During this introduction, all TDTP students will be informed that their participation in the study is voluntary and refusal to enrol or withdraw after study enrollment will not affect their subsequent TDTP participation or outcomes. After this introduction, each individual will be provided with the contact information (email and telephone number) for a study team member that can be reached to further discuss the study and possible enrollment. For those individuals who contact the study team member, an in-person meeting or audio/video teleconference will be scheduled. During this meeting, the study team member will discuss the study rationale, objectives, participant responsibilities, data collection, risks and benefits. During this meeting, the study team member will encourage and answer study-related questions. For interested individuals, the study team member will review the informed consent form (ICF) and answer all questions. Interested individuals will be provided with a paper/electronic copy of the ICF to review, and a subsequent follow-up in-person or audio/video teleconference meeting in 72 hours (business days) will be scheduled between the study team member and the interested individual to determine their interest to enroll in the TeachMeToBuild study. All TDTP students will be reminded by the study team member during the meetings that study participation is voluntary and refusal to enrol or withdraw after study enrollment will not adversely affect their subsequent TDTP participation or outcomes. To withdraw from the study, the participant will inform the case manager who will then inform the study team members.

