### 18.12 Routinely collected data

Any clinical encounters with a healthcare provider for any reason may require the collection of personal health information, such as Ontario Health Insurance Plan number, along with other information as dictated by the healthcare provider, healthcare facility, and diagnostic and therapeutic care plan. The PHIPA-compliant storage and transmission of this routinely collected clinical data will be the responsibility of the health information custodian. This study has no requirements for the *a priori* collection of any routinely collected clinical data.

Other routinely collected data specific to the TDTP includes daily attendance and program completion. The Training Program Coordinator is responsible for this data collection. The daily attendance data will be collected using the Distress Thermometer screening tool. Program completion data will be collected at the end of the 12-week TDTP and entered into the electronic case report form in REDCap by study personnel.

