#### 18.13a Foundational skills

Complete essential skills self-assessment for the trades questionnaire (28). There are 9 foundational skills identified in the questionnaire, each containing statements that require the apprentice to answer *yes, somewhat or no.*  For any skills sub-domain in which the apprentice answers *somewhat* and/or *no* in less than 5 statements, the apprentice is considered to possess a *strength* in that foundational skill. A cumulative score of the number of foundational skills that each apprentice possesses (out of 9) will be calculated and used as a baseline variable. Each apprentice will be asked to complete this survey as part of the routine orientation process. The survey link will be provided to each apprentice and all results will be stored in REDCap using a unique identifier number.

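### Consent on day 0 and screening from day 1 (Section 13) cannot follow the two-meeting consent process of Section 15 if orientation is at T0; about 3 of 48 program days then count without possible tool use.

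*Protocol*

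**What the plan says.** - **Schedule (Protocol, Section 13).** Cohort randomization is at day -7. The row "Informed Consent" and the foundational skills survey are both marked at T0, day 0. Distress Thermometer screening and attendance run from day 1.
- **Orientation (Section 18.13a).** On the skills survey: "Each apprentice will be asked to complete this survey as part of the routine orientation process". Together with the Section 13 entry, this places orientation at T0.
- **Consent process (Section 15).** Students in cohorts randomized to the tool "will be introduced to the TeachMeToBuild study during their initial TDTP orientation". The next step is theirs: "For those individuals who contact the study team member, an in-person meeting or audio/video teleconference will be scheduled". The consent form is reviewed at that meeting, and then "a subsequent follow-up in-person or audio/video teleconference meeting in 72 hours (business days) will be scheduled" to establish whether the student enrols.
- **Consent comes first (Section 10).** "Participants must provide written, informed consent before any study procedures occur".
- **Outcome windows.** Section 12.11 measures attendance from the program start date: "The potential number of AFDs for each apprentice is the cumulative number of program days that the apprentice is alive during the 12-week TDTP", up to 48. Section 12.27 divides completed screens by all program days. Neither makes allowance for the date of consent.
- **Who is asked (Section 16.3).** Consent is sought only in the cohorts allocated to the tool.

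**The concern.** Consent on day 0 and screening on day 1 leave no room for student-initiated contact, a first meeting and a wait of 72 business-day hours, if all of these begin at an orientation held on day 0. Because no study procedure may precede consent, the tool cannot be in use on the first program days. Section 11.12 nevertheless asks for daily use throughout the 12 weeks, and Sections 12.11 and 12.27 count from the program start.

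Three things are at stake:

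- The effect of the tool on attendance, a primary outcome, is averaged over days on which the tool could not act.
- Compliance (12.27) is understated for a reason unrelated to the apprentice's behaviour.
- Sections 11.3 and 15 tie a payment and a prize draw to completing at least 90% of daily screens. A long enough delay could put that out of reach.

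**Working it through.** **Inputs from the Protocol**

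- Program days are Monday to Thursday for 12 weeks (12.11): 12 x 4 = 48, which reproduces the stated maximum.
- The wait between the two meetings is 72 hours in business days (15), read here as 3 business days.
- Randomization is 1 week before the start (13, 16.3).
- The incentive threshold is 90% of daily screens (11.3, 15).

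**Assumptions, because the Protocol gives no figure**

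- The program starts on a Monday.
- The lag from orientation to the first meeting is L business days. Section 15 sets none, so L = 0 gives the minimum.
- The screen is due before the day's session (11.12). The consent day itself may or may not be lost, so both counts are shown.

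**Formula.** Consent day = orientation day + L + 3 business days. Lost days = program days from the start up to consent, without and with the consent day.

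**Orientation at T0, first meeting the same day (L = 0)**

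| Orientation | Consent | Days lost | Share of 48 |
|---|---|---|---|
| First Monday | Thursday, week 1 | 3 (4 with consent day) | 6.3% (8.3%) |
| Friday before | Wednesday, week 1 | 2 (3 with consent day) | 4.2% (6.3%) |

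The loss that follows from the text is therefore about 3 days, with a range of 2 to 4 (4.2% to 8.3%).

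**Slower first meeting.** With orientation on the first Monday, L = 2 loses 4 to 5 days and L = 3 loses 5 to 6. With orientation on the Friday before, L = 3 loses 4 to 5 and L = 4 loses 5 to 6.

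**Compliance ceiling under 12.27 for an apprentice who completes every possible screen**

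- 3 days lost: 45/48 = 93.8%
- 4 days lost: 44/48 = 91.7%
- 5 days lost: 43/48 = 89.6%, below 90%

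A documented reason for skipping a screen counts as completion (11.3, 12.27). It is entered in the tool, so it does not help before the apprentice has access.

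**Dilution.** Suppose the tool has no effect on days without it and raises attendance by 5 points on the other days. Effect over the window = 5 x (48 - lost)/48.

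- 2 days lost: 5 x 46/48 = 4.8 points
- 3 days lost: 5 x 45/48 = 4.7 points
- 4 days lost: 5 x 44/48 = 4.6 points

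**Can the process fit before the start?** With orientation on the Monday of the week before (day -7), L = 0 or 1 loses no days and L = 2 loses 0 to 1. With orientation on the Tuesday, only L = 0 is sure to lose none. The process can fit, but only if orientation comes early in that week and the first meeting follows almost at once.

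**The case against.** **Orientation is never dated.** Its place at T0 is inferred from the skills survey. Section 16.3 has students told of the allocation after randomization, with consent to follow, which leaves about five business days before the start. T0 may also be just a baseline column, since Section 13 has none between day -7 and day 0. This stands in part: an early orientation avoids the loss. But it departs from the T0 placement in Section 13, and the Protocol does not call for it. The sections need reconciling on either reading.

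**Attendance recording.** A reader might infer that days before consent go unrecorded and count as absences, because "The daily attendance data will be collected using the Distress Thermometer screening tool". The documents do not support this. Section 18.12 classes attendance as routine program data for which the Training Program Coordinator is responsible. Section 18.11 lists it under the Case Manager, and 12.11 credits a day on staff documentation. Control cohorts need the same record and are not asked for consent at all. Consent is not shown to gate recording.

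**Larger losses.** A reader might infer up to 8 lost days (8/48 = 16.7%). That needs a lag of about 5 to 7 business days before the first meeting, and the Protocol states no lag. A further inference, that early leavers weaken the completion result, has no figure behind it, since the Protocol gives no drop-out timing.

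**The dilution is small and may belong to the estimand.** Section 14.1 sets its 5% difference on the proportion of absence-free days over the whole window, not on exposed days. In a pragmatic trial, slow uptake can be part of the effect of offering the tool. This is fair. The 4.7-point figure is an illustration under a stated assumption, not a correction to the power table. It is also a reason to keep one attendance window for all cohorts. It does not justify a delay built into the consent process that the schedule says is absent.

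**Conclusion.** The inconsistency is real. If orientation is at T0, consent on day 0 with screening from day 1 cannot be achieved under Section 15. At least about 3 of 48 program days (2 to 4 by calendar reading) are then counted in the tool arms' attendance window and compliance denominator without possible tool use.

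The effect on attendance is modest: 5 points on exposed days becomes about 4.7 over the window at 3 lost days. Compliance is capped at about 94% in that case. It falls below the 90% incentive threshold only at 5 or more lost days, and only if the incentive uses the 12.27 denominator, which the Protocol does not say.

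The conclusion rests on orientation at T0, a Monday start and 72 business-day hours read as 3 business days. It does not extend to unrecorded attendance or to losses of a week or more. It is worth correcting because the remedy is cheap and changes how many days the tool is in use.

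**What to change.** 1. **Reconcile Sections 13 and 15.** Date orientation, or at least the study introduction. Give the introduction and the consent form early in the week between cohort allocation (day -7) and the start date, so that the follow-up meeting is held by day 0. With a Monday start, a first meeting by the Tuesday of that week puts the follow-up on the Friday.
2. **Section 12.27.** For anyone who consents later, count compliance from the first program day after consent, and say whether the 90% incentive uses the same denominator.
3. **Section 12.11.** Keep the attendance window from the program start in every cohort. Starting it at consent would give the tool cohorts a different window from the control cohorts, which have no consent date.

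The cost is a change of timing in Section 15, a matching entry in Section 13 and a sentence in 12.27. Section 16.2 already requires registration of the whole cohort before the allocation is released, so the students are known by then. The downside is that study staff must reach registered students before the program begins.

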# 16 Allocation

## 16.1 Sequence generation

Cohorts will be randomly assigned to either BCM or ICM^1x^ (Figure 1) with a 1:1:1:1 allocation schema as per a computer-generated randomisation schedule stratified by site using permuted blocks of size 4 in each strata. A single block size was chosen to accommodate potentially different cohort numbers resulting from variation in the cohort sample sizes. The block size will not be disclosed to ensure concealment.

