# 8 Design

The *TeachMeToBuild* trial is designed as a pragmatic, open-label, 2x2 factorial, cluster randomized, controlled, superiority study. Each cohort (cluster) will be randomized in a 1:1 allocation ratio to the self-report tool for distress using a stratified, permuted-block group schema according to the following strata:

1) Study site (Sudbury, Barrie)

The MH&A fit-for-purpose service will only be available to apprentices located at the Barrie site.

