# 17 Masking

This is an open-label, pragmatic study so neither study participants nor Community Builders® nor study personnel, including data analysts, will be masked to the allocation.

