# 28 Declaration of interests

GD and CS have never received any salary support or grants, honoraria, paid consultancies or service on advisory boards, receipt of patents or patents pending, ownership of stocks or options from Community Builders Construction or Alectra. SB is a paid employee of Community Builders Construction. Community Builders Construction has received a Federal grant from the Youth Employment and Skills Strategy program.

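### A single block size of 4 per site, printed in the protocol, lets up to a third of cohort allocations be deduced before registration closes

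*Protocol*

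**What the plan says.** **Sequence.** Protocol 16.1 specifies a "computer-generated randomisation schedule stratified by site using permuted blocks of size 4 in each strata". It gives this reason for one size: "A single block size was chosen to accommodate potentially different cohort numbers resulting from variation in the cohort sample sizes". It then states: "The block size will not be disclosed to ensure concealment".

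**What is randomised.** Section 8: "Each cohort (cluster) will be randomized in a 1:1 allocation ratio to the self-report tool for distress". The other factor is fixed by location: "The MH&A fit-for-purpose service will only be available to apprentices located at the Barrie site".

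**Who sees allocations.** Under section 17, "neither study participants nor Community Builders® nor study personnel, including data analysts, will be masked to the allocation". Under 16.3 the Training Program Coordinator requests each randomisation one week before the cohort starts, is told the result and passes it to the students.

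**Who chooses apprentices.** Under section 15 Community Builders interviews applicants: "Successful candidates must demonstrate that they are a good fit for the TDTP".

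**Who may know the block size.** Section 23.3 provides that case managers are trained on every aspect of the protocol and on the randomisation system. Section 28 adds that one person declaring interests "is a paid employee of Community Builders Construction".

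**Safeguard.** Under 16.2 an independent coordinator alone holds the list and releases a cohort's code only once all its students are registered.

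**The concern.** Section 16.1 relies on an undisclosed block size for concealment, but it prints that size. Anyone with the protocol and a record of the site's past allocations can work out some later ones. The delayed release in 16.2 hides the current code. It does not stop inference from earlier, openly known allocations in the same block, and registration is the step that such inference could influence.

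What is at stake is selection into the only factor that is randomised. Staff who can foresee an allocation could, even without intending it, affect who joins a cohort or when it starts, and a whole cohort is allocated at once. The completion and employment models (20.11b, 20.11c) list no baseline covariates. The attendance model (20.11a) adds unbalanced baseline variables only in a sensitivity analysis. The main models as written would therefore not correct a resulting imbalance.

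The stated reason for one block size does not help, because varying sizes also accommodate any number of cohorts.

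**Working it through.** The protocol gives no predictability figure. Its number of cohorts does reproduce.

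**1. Cohorts per site (14.1).** 400 apprentices over two sites is 200 per site. With 6 to 10 per cohort, 200/10 = 20 and 200/6 = 33.3, rounded up to 34. The protocol states 20 to 34.

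**2. Arms per site.** The mental health and addictions service is fixed by site, so each site's list has two arms, 2 + 2 per block of 4. Section 16.1 also writes the ratio as 1:1:1:1. Four arms in a block of 4 would make 1/4 deducible, but that reading is impossible within a site.

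**3. One block.** There are 6 equally likely orders. An allocation is deducible when only one arm has places left. A best guess names the arm with more places left.

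| Position | P(deducible) | P(best guess right) |
|---|---|---|
| 1 | 0 | 1/2 |
| 2 | 0 | 2/3 |
| 3 | 1/3 (first two the same: 2 of 6 orders) | 2/3 |
| 4 | 1 | 1 |
| Sum | 4/3 | 17/6 |

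The deducible share is (4/3)/4 = 33.3%. The best-guess rate is (17/6)/4 = 17/24 = 70.8%, against 50% with no information.

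**4. Per site, cohorts filled one after another.**
- 20 cohorts are 5 full blocks: 5 × 4/3 = 6.7 (33.3%).
- 34 cohorts are 8 full blocks plus 2. The first two positions of a block are never deducible, so 8 × 4/3 = 10.7 (31.4%). Best guesses: 8 × 17/6 + 1/2 + 2/3 = 23.8 of 34 (70.1%).
- Both sites: 2 × 6.7 = 13.3 to 2 × 10.7 = 21.3.

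**5. Sensitivity to cohort size.** Section 5.15 anticipates classes of 8 to 15, which gives 200/15 = 13.3 (14) to 200/8 = 25 cohorts per site. Then 3 × 4/3 = 4.0 of 14 to 6 × 4/3 = 8.0 of 25 are deducible.

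**6. Sensitivity to overlap (assumption).** Suppose cohorts at a site fill in pairs, positions 1 and 2 together and then 3 and 4 together. The second pair is deducible only if the first two matched, so 2 × 1/3 = 2/3 per block. That is 1/6 of a full block: 5 × 2/3 = 3.3 of 20, or 8 × 2/3 = 5.3 of 34.

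**7. Varying block sizes.** Simulation at 34 cohorts per site, with an observer who knows the set of sizes but not their order:

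| Block sizes | Certain | Best guess right |
|---|---|---|
| Fixed 4 | 31.4% | 70.2% |
| 2, 4, 6 at random | 3.9% | 70.0% |
| 4, 6, 8 at random | 2.4% | 67.5% |

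At 20 cohorts, sizes 4, 6 and 8 give much the same: about 2% certain and about 67% right.

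**The case against.** **Known versus deducible.** A reader might infer that a third of allocations are known in advance. The protocol does not support that. Deduction needs the block size, a full record of the site's past allocations, and sequential filling. Nothing says that cohorts fill one at a time. At 12 weeks each, 20 to 34 back-to-back cohorts would take 20 × 12/52 = 4.6 to 34 × 12/52 = 7.8 years. The budget (section 34) has 3 years of technical support and 90 audit hours at 15 per 6 months, which is also 3 years. Some overlap is therefore plausible, though this is an inference. The objection stands, and one third is a ceiling.

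**Published block size.** A reader might also infer that the size is public during recruitment. Section 32 promises release of the protocol no later than 3 years after closure and does not say when before then. Section 28 shows that one declarant works for Community Builders, not that this person selects apprentices. The better-supported route is the staff training in 23.3.

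**Harm.** The protocol documents no motive for steering, and the minimum standard of fit in section 15 is modest: interest in construction and basic language skills. The point is that the design permits selection, not that selection will happen. Individual consent after allocation is announced (15, 16.3) is a separate and more direct route to selection, which this change leaves untouched.

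**Value of the fix.** Varying blocks remove certainty but barely reduce the best-guess rate. This stands. Larger blocks also loosen balance over calendar time, which matters because the primary models include year-quarter and its interaction with each intervention.

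**Conclusion.** The point holds as an internal contradiction and an avoidable weakness in concealment. Section 16.1 prints the block size that it says will be withheld, and the release rule in 16.2 does not cover deduction from earlier allocations. Up to 6.7 of 20 to 10.7 of 34 allocations per site can be deduced before registration closes, about 13 to 21 overall, with a best-guess rate of about 70 to 71%. These figures assume two arms per site, sequential filling, the cohort sizes in 14.1, and staff who know both the size and the site's past allocations. With the class sizes in 5.15 the range is about 4 to 8 per site, and overlap lowers it further. The documents do not show that anyone would use this knowledge, and the size of any resulting bias cannot be calculated from them.

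**What to change.** Before the first cohort is randomised:

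- **16.1:** generate each site's tool-versus-no-tool sequence with randomly varying block sizes, for example 4, 6 and 8. Remove the sizes from the protocol and keep them only in a restricted file held by the independent study coordinator. Delete the reason given for a single size.
- **16.2:** keep the release rule, and add that each cohort's completed registration is time-stamped in REDCap before its code is released. The time stamp is the only new element; it makes the existing rule auditable.

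Do not add a ban on moves between cohorts. Section 11.2 provides for some apprentices to be withdrawn and enrolled in a later cohort, and a blanket ban would contradict it.

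**Cost:** one regenerated list and short edits to two sections. Section 1.1 records recruitment as not yet started. If enrolment stops mid-block, the arms at a site could differ by up to 4 cohorts (half of a block of 8) rather than 2 (half of a block of 4), and balance over calendar time is slightly looser. **Gain:** certain allocations fall from about a third to about 2 to 3%, with only a small drop in the best-guess rate, to about 67%. This is a cheap improvement, not complete protection.
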